## Abstract

**Background**: Performing and maintaining high-altitude cardiopulmonary resuscitation (CPR) could pose a significant physical challenge for rescuers. The objective of this study is to analyse the effects of reducing the oxygen fraction at altitudes of 3000 m and 5000 m above sea level (asl), with and without conditioning to hypoxia, on the quality of resuscitation performed in adults. **Methods**: An analytical before–after study in which 56 students with a Degree in Nursing between 18 and 30 years old perform 10 min of resuscitation on a mannequin at different altitudes (670, 3000 and 5000 m asl) will be carried out. Subsequently completing an intermittent hypoxia conditioning programme, the participants will perform the resuscitation manoeuvres at previously referenced altitudes. Sociodemographics, CPR quality, self-perception CPR, adequate anthropometric data, physical condition, blood tests, oxygenation in muscular tissue, biceps, brachii and erector spinae, subjective perception of effort, anxiety levels and quality of resuscitation will be measured in all participants at different altitudes. **Discussion:** Although CPR is a submaximal effort manoeuvre, it is subject to being performed by anyone without motor disabilities. Our study will also provide evidence as to whether this characteristic continues to hold true in a hostile environment such as medium and high altitudes. Our study aims to demonstrate that the improvement in physical performance and recovery capacity induced by intermittent hypoxia conditioning programmes increases the quality of CPR in prolonged cardiac arrests and in adverse conditions, such as at high altitudes. The proposed study will contribute as a novelty to the estimation of the influence of high altitudes and conditioning on performing basic CPR manoeuvres. If the hypothesis turns out to be true, recommendations about the practice of moderate-intensity physical exercise could be incorporated into the CPR guidelines as one of the important aspects in the training of rescuers to conduct CPR.

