### 2.3. Sample Size

Participants will be recruited using a convenience sampling approach among eligible nursing students. After baseline assessment, participants will be randomly allocated to one of two parallel groups: (1) an intermittent hypoxia conditioning group or (2) a sham control group. The random allocation sequence will be generated using a computer-based random number generator with a 1:1 allocation ratio. To ensure balance between groups, block randomisation will be applied with variable block sizes. Allocation concealment will be guaranteed using sealed, opaque, and sequentially numbered envelopes prepared by an independent researcher not involved in participant recruitment or assessment.

The assignment of participants to study groups will be conducted by a researcher not involved in outcome assessment or data analysis. Due to the nature of the intervention, participants and intervention supervisors cannot be blinded to group allocation. However, outcome assessors and data analysts will be blinded to group allocation to minimise detection and analysis bias. Specifically, outcome assessors will evaluate CPR performance using anonymised, coded data with no group identifiers, ensuring that group allocation remains concealed. The randomisation sequence generation and allocation concealment will be performed by an independent researcher, who will have no involvement in outcome assessment or data analysis.

To control for potential confounding variables, a multivariate model (multiple linear regression) will be applied. The change in Q-CC following the intervention will be considered as the dependent variable, while potential confounders (e.g., age, sex, BMI, physical fitness, and blood parameters) will be included as covariates. Interactions between these variables and altitude conditions will also be explored.

The sample size calculation is based on an expected baseline proportion of correct compressions of 52%, according to a previous study [16]. Using Epidat 4.2 software, assuming paired comparisons, a 95% confidence level, and 80% statistical power, a total of 56 participants is required to detect an increase in the proportion of correct compressions to 78%. To account for potential dropouts or non-responses, the total sample size will be increased by 10%.

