### 2.4. Interventions

#### Training CPR Programme

Participants without prior CPR training will undergo a standardised training programme designed in accordance with current European Resuscitation Council (ERC) guidelines. The training programme will consist of: (1) a theoretical session (60 min), including basic life support principles, recognition of cardiac arrest, and CPR sequence; (2) a practical hands-on training session (120 min), during which participants will practice chest compressions and ventilations using feedback-enabled mannequins under instructor supervision; and (3) a supervised skill consolidation session (30 min) focused on correcting technique and ensuring adherence to guideline criteria (compression depth, rate, recoil, and ventilation quality). The total training duration will therefore be approximately 3.5 h. Training will be delivered by certified instructors following a structured protocol to ensure standardisation across participants. Objective feedback devices will be used to facilitate motor skill acquisition and improve CPR quality performance. This training duration is consistent with previous literature demonstrating that structured sessions of at least 2–4 h are required for adequate acquisition of basic CPR skills and retention of performance quality.

Stage 1: An initial baseline assessment will be carried out in all participants (*n* = 56), consisting of collection of parentage data and anamnesis, as well as the measurement of physiological variables at rest (resting electrocardiogram and pulmonary function test), which will allow ruling out the existence of pathologies that contraindicate the performance of ergospirometry. Other measurements include diastolic blood pressure (DBP) and systolic blood pressure (SPB), anthropometry, ergospirometry to determine the maximal HR achieved and VO_2_max, muscle strength, and initial hypoxia tolerance test.

Stage 2: All participants (*n* = 56) will perform 10 uninterrupted minutes of CPR (with a CC/ventilation ratio of 30:2) on a mannequin with a quality measurement device for CTE and ventilations (Q-CPR) in the following situations:

Test M1: CPR at 670 m asl, FiO_2_ of 0.21.

Test M2: CPR at normal pressure simulating 3000 m asl, FiO_2_ of 0.14.

Test M3: CPR at normal pressure simulating 5000 m asl, FiO_2_ of 0.11.

Prior to M2 and M3, each participant will have an acclimatisation period of 10 min to FiO_2_ corresponding to each of the altitudes.

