To minimise the effect of fatigue between tests, each participant will have a 24 h rest period.

Stage 3: Participants assigned to the intervention group will undergo a standardised intermittent hypoxia conditioning programme (13 sessions, 45–75 min/session), including alternating cycles of hypoxia (FiO_2_ progressively reduced from 0.14 to 0.11) and normoxia, resulting in a total hypoxic exposure of approximately 728 min. The control group will undergo a sham protocol consisting of identical session structure and duration under normoxic conditions. Three to five weekly sessions will be held according to tolerance and the iAltitude^®^ protocol [42].

Stage 4: After the intervention, all the participants (*n* = 56) will perform three uninterrupted 10 min sessions of CPR: the first at 670 (P1), the second (P2) at 3000, and the third (P3) at 5000 m asl. To minimise the effect of fatigue between tests, each participant will have a 24 h rest period [42]. The criteria for completing the different CPR tests will be determined by reaching 10 min or by the physical and/or physiological limitations of the rescuer (physical exhaustion or pain, SatO_2_ < 75).

Throughout all stages, heart rate and peripheral oxygen saturation (SpO_2_) will be continuously monitored using an ear clip pulse oximeter. The training programme instructs the participant to breathe ambient air if the SpO2 level exceeds the limit specified in Table 1 (Lim SpO2). During hypoxia tests, as well as during conditioning, a nurse and/or a doctor with experience in emergency care will be present.

To minimise potential confounding due to independent practice, participants will be explicitly instructed not to perform any additional CPR training or practice outside the study protocol during the study period.

The pre-conditioning protocol for high-altitude exposure was designed based on experience and knowledge regarding the use of normobaric intermittent hypoxia (IHT) to enhance sporting performance. To this end, the following data were collected from each participant: age, sex, height, weight, body fat percentage, sport practised (if applicable), number of weekly training sessions, time spent training, and ability to perform CPR manoeuvres in accordance with the study design.

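### The article requires 56 participants and adds 10% for losses, yet gives n = 56 in the abstract and at Stages 1, 2 and 4, so the enrolment target is contradictory.

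*Protocol article*

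**What the plan says.** Section 2.3 (Sample Size) sets out the calculation. "The sample size calculation is based on an expected baseline proportion of correct compressions of 52" per cent. The comparison is taken as paired, with confidence of 95% and power of 80%. The result is stated as follows: "a total of 56 participants is required to detect an increase in the proportion of correct compressions to 78" per cent. The next sentence adds the allowance: "To account for potential dropouts or non-responses, the total sample size will be increased by 10" per cent. The same section allocates participants by a "computer-based random number generator with a 1:1 allocation ratio".

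The counts elsewhere in the article are:

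- Abstract: "56 students with a Degree in Nursing between 18 and 30 years old perform 10 min of resuscitation".
- Section 2.4, Stage 1 (entry assessment): "An initial baseline assessment will be carried out in all participants (*n* = 56".
- Section 2.4, Stage 2 (CPR before conditioning): all participants, again 56.
- Section 2.4, Stage 3 (conditioning): no count.
- Section 2.4, Stage 4 (CPR after conditioning): "After the intervention, all the participants (*n* = 56) will perform three uninterrupted 10 min sessions of CPR".

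Section 2.1 lists, among its exclusion criteria, altitude intolerance identified from physiological measurements while CPR is performed at simulated altitude.

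**The concern.** The number the power calculation needs, the number entering at Stage 1 and the number tested at Stage 4 are all 56. They cannot all be right if the 10% allowance is real. Either more than 56 enter, and the abstract and the Stage 1 and Stage 2 counts are wrong, or 56 enter, and any loss takes the trial below its stated requirement.

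Some loss is to be expected on the article's own terms. Section 2.3 provides for it. Section 2.1 names a route by which people who have passed the Stage 1 assessment can still be excluded, since CPR at simulated altitude first takes place in Stage 2. Participants must also complete a conditioning or sham programme and a second set of CPR tests.

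Staff need a single recruitment target, and the randomisation list and envelopes need a single length. At present a reader could take either 56 or 62 from the article.

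**Working it through.** **Inputs.** From Section 2.3: proportions 0.52 and 0.78 (difference d = 0.26), paired comparison, 95% confidence, 80% power, required total 56, allowance 10%, allocation 1:1. Not stated, so assumed here: a two-sided test, and independence within pairs.

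**Step 1. Reproduce the 56.** Under independence the discordant cells are 0.52 × 0.22 = 0.1144 and 0.78 × 0.48 = 0.3744, so the discordant proportion is pd = 0.4888. The McNemar normal-approximation formula is

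n = [1.96·√pd + 0.8416·√(pd − d²)]² / d²

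= [1.96 × 0.6991 + 0.8416 × 0.6490]² / 0.0676 = 1.9165² / 0.0676 = 54.3, so 55 pairs.

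With pd = 0.50 the result is 55.6, so 56. The stated 56 is therefore reproduced as the requirement *before* any allowance. If 56 already contained the allowance, the base would be about 50 to 51 (56 × 0.9 = 50.4; 56/1.10 = 50.9).

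**Step 2. Apply the article's own rule.** 56 × 1.10 = 61.6, so 62, or 31 per arm if all 62 are randomised 1:1.

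**Step 3. Compare with the printed counts.**

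| Place | Printed | If 62 enrol | If 56 enrol and 10% are lost |
|---|---|---|---|
| Abstract | 56 | 62 | 56 |
| Stage 1 | 56 | 62 | 56 |
| Stage 2 | 56 | 62 | 56 |
| Stage 4 | 56 | about 56 (62 × 0.9 = 55.8) | about 50 (56 × 0.9 = 50.4) |

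For simplicity the table places all loss between Stages 2 and 4. Neither scenario matches the printed column.

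**Step 4. Power if only 56 enter.** Power = Φ{[d·√n − 1.96·√pd] / √(pd − d²)}.

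- pd = 0.4888, n = 56: (1.946 − 1.370)/0.649 = 0.887, so about 81%.
- pd = 0.4888, n = 50: (1.838 − 1.370)/0.649 = 0.721, so about 76%.

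Standard errors rise by √(56/50) = 1.058, about 6%.

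**Step 5. Sensitivity to the unstated discordance.**

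| pd | Pairs needed for 80% power | Power at 56 | Power at 50 |
|---|---|---|---|
| 0.45 | 49.8 | 85% | 80% |
| 0.4888 | 54.3 | 81% | 76% |
| 0.55 | 61.4 | 76% | 71% |

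For pd = 0.45, √pd = 0.6708 and √(0.45 − 0.0676) = 0.6184. At n = 56, (1.946 − 1.315)/0.6184 = 1.020; at n = 50, (1.838 − 1.315)/0.6184 = 0.847.

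**The case against.** The strongest reply is that the allowance is not absent. Section 2.3 says plainly that the total will be raised, and 56 elsewhere may simply be the required evaluable sample repeated without the inflated figure. On that reading the defect is one of labelling. This reading could fit Stage 4. It does not fit Stage 1, which is the entry assessment, comes before randomisation and is described as covering all participants. It fits the abstract poorly too. What stands is that the article does intend an allowance. A reader might infer from the repeated 56 that the trial plans for zero loss, and Section 2.3 contradicts that.

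Several stronger readings are also not supported:

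- *The error affects every stage and the flow chart.* Stage 3 gives no count, and Figure 1 is not visible in the text reviewed.
- *The 10% rule is itself miscalculated, because 56/0.9 = 62.2 gives 63.* The article says only that the total is raised by 10%, not that 56 will remain after a 10% loss. The difference is 0.2 of a participant (62 × 0.9 = 55.8), and 62 splits evenly 1:1. This is a matter of convention.
- *The test-ending criteria in Stage 4 and the pregnancy contraindication in Section 2.1 are sources of dropout.* The former end a CPR test and the latter bars inclusion; neither is stated as withdrawal from the study.
- *The power figures describe the comparison between arms.* They do not. They follow the paired calculation in Section 2.3. Whether that calculation suits a two-arm randomised comparison is a separate question.

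The reply is also right that the numerical consequence is modest, and that it arises only if enrolment stops at 56 and the full 10% is lost.

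**Conclusion.** The inconsistency holds and can be checked from the article alone: Section 2.3 implies 62 enrolled, while the abstract and Stages 1, 2 and 4 print 56. The order of the sentences in Section 2.3 is enough to show that 56 is the figure before the allowance. The re-derivation (55 to 56 pairs) agrees but is only supportive, because the within-pair correlation is not given.

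If enrolment stops at 56 and 10% are lost, about 50 complete, six short of the stated requirement. Power on the plan's paired comparison then falls from about 81% to about 76%, assuming a two-sided 5% McNemar test and independence within pairs. With less discordance (0.45) the power at 50 pairs is still about 80%; with more (0.55) it is about 71%, but 56 would then not have reached 80% either. The loss is small. The reason to act is that the recruitment target is contradictory and the correction is cheap.

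**What to change.** Choose one of two courses and apply it throughout.

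1. **Keep the allowance.** State an enrolment target of 62 in Section 2.3 (31 per arm if all are randomised), use 62 in the abstract and at Stages 1 and 2, and label 56 at Stage 4 as the expected number of completers. Check that Figure 1 agrees.
2. **Enrol only 56.** Delete the 10% sentence and restate the power for about 50 completers, giving the discordant proportion or within-pair correlation assumed.

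The first course costs a few words and no participants beyond those Section 2.3 already plans. The second costs a slightly lower stated power.

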### 2.4. Interventions

#### Training CPR Programme

Participants without prior CPR training will undergo a standardised training programme designed in accordance with current European Resuscitation Council (ERC) guidelines. The training programme will consist of: (1) a theoretical session (60 min), including basic life support principles, recognition of cardiac arrest, and CPR sequence; (2) a practical hands-on training session (120 min), during which participants will practice chest compressions and ventilations using feedback-enabled mannequins under instructor supervision; and (3) a supervised skill consolidation session (30 min) focused on correcting technique and ensuring adherence to guideline criteria (compression depth, rate, recoil, and ventilation quality). The total training duration will therefore be approximately 3.5 h. Training will be delivered by certified instructors following a structured protocol to ensure standardisation across participants. Objective feedback devices will be used to facilitate motor skill acquisition and improve CPR quality performance. This training duration is consistent with previous literature demonstrating that structured sessions of at least 2–4 h are required for adequate acquisition of basic CPR skills and retention of performance quality.

Stage 1: An initial baseline assessment will be carried out in all participants (*n* = 56), consisting of collection of parentage data and anamnesis, as well as the measurement of physiological variables at rest (resting electrocardiogram and pulmonary function test), which will allow ruling out the existence of pathologies that contraindicate the performance of ergospirometry. Other measurements include diastolic blood pressure (DBP) and systolic blood pressure (SPB), anthropometry, ergospirometry to determine the maximal HR achieved and VO_2_max, muscle strength, and initial hypoxia tolerance test.

Stage 2: All participants (*n* = 56) will perform 10 uninterrupted minutes of CPR (with a CC/ventilation ratio of 30:2) on a mannequin with a quality measurement device for CTE and ventilations (Q-CPR) in the following situations:

Test M1: CPR at 670 m asl, FiO_2_ of 0.21.

Test M2: CPR at normal pressure simulating 3000 m asl, FiO_2_ of 0.14.

Test M3: CPR at normal pressure simulating 5000 m asl, FiO_2_ of 0.11.

Prior to M2 and M3, each participant will have an acclimatisation period of 10 min to FiO_2_ corresponding to each of the altitudes.

To minimise the effect of fatigue between tests, each participant will have a 24 h rest period.

Stage 3: Participants assigned to the intervention group will undergo a standardised intermittent hypoxia conditioning programme (13 sessions, 45–75 min/session), including alternating cycles of hypoxia (FiO_2_ progressively reduced from 0.14 to 0.11) and normoxia, resulting in a total hypoxic exposure of approximately 728 min. The control group will undergo a sham protocol consisting of identical session structure and duration under normoxic conditions. Three to five weekly sessions will be held according to tolerance and the iAltitude^®^ protocol [42].

Stage 4: After the intervention, all the participants (*n* = 56) will perform three uninterrupted 10 min sessions of CPR: the first at 670 (P1), the second (P2) at 3000, and the third (P3) at 5000 m asl. To minimise the effect of fatigue between tests, each participant will have a 24 h rest period [42]. The criteria for completing the different CPR tests will be determined by reaching 10 min or by the physical and/or physiological limitations of the rescuer (physical exhaustion or pain, SatO_2_ < 75).

Throughout all stages, heart rate and peripheral oxygen saturation (SpO_2_) will be continuously monitored using an ear clip pulse oximeter. The training programme instructs the participant to breathe ambient air if the SpO2 level exceeds the limit specified in Table 1 (Lim SpO2). During hypoxia tests, as well as during conditioning, a nurse and/or a doctor with experience in emergency care will be present.

To minimise potential confounding due to independent practice, participants will be explicitly instructed not to perform any additional CPR training or practice outside the study protocol during the study period.

The pre-conditioning protocol for high-altitude exposure was designed based on experience and knowledge regarding the use of normobaric intermittent hypoxia (IHT) to enhance sporting performance. To this end, the following data were collected from each participant: age, sex, height, weight, body fat percentage, sport practised (if applicable), number of weekly training sessions, time spent training, and ability to perform CPR manoeuvres in accordance with the study design.

As indicated in the text and illustrated in Figure 2, the study protocol comprises four stages. The first stage involves performing a hypoxia tolerance test. The second stage involves carrying out CPR tests without hypoxia conditioning at different altitudes. The third stage consists of 15 sessions of IHT conditioning. Finally, the fourth stage involves performing CPR tests at the specified altitudes.

The Hypoxic Training Index (HTI) and the Hypoxic Recovery Index (HRI) are monitored in both phase 1 and phase 3. The HTI is a measure of the cumulative hypoxic stress experienced during a session and over successive sessions of the protocol. This index is calculated as an integral value of SPO2 readings below 90%. The HRI is used as an indicator of the individual’s recovery capacity following hypoxic stress during a session, and cumulatively across subsequent sessions of the protocol. It is calculated during periods when SPO2 readings are above 90%, and its value increases more rapidly the better an individual recovers from the hypoxic load to which the individual is exposed. The HTI is calculated as the area under the curve (AUC) of SpO_2_ values below 90%, expressed as %·min, representing the cumulative magnitude and duration of hypoxic stress. The HRI is calculated as the area above 90% SpO_2_ during recovery periods (also expressed as %·min), reflecting the extent and rate of reoxygenation.

In order to complete the designed IHT pre-conditioning protocol, participants will need to complete the 15 sessions detailed in Table 1. These sessions will be conducted under the supervision of a trained supervisor who will be responsible for ensuring that: (1) throughout all sessions, participants are monitored via pulse oximetry and follow the instructions provided by the iAltitude software (Hypoxiahome Trainer 4.1) at all times in order to ensure safety and achieve the expected results; (2) a minimum interval of at least 24 h is maintained between sessions, with no more than 72 h elapsing between them; (3) more than 2 h have elapsed between the participant’s last meal and the start of the session; and (4) the breathing pattern during the sessions remains natural. The breathing rate should not be increased, and the breaths should not be deep, so that the amount of oxygen inhaled corresponds to the level required for the session, based on the specified FiO_2_ percentage.

SPO2 Limit: This value indicates how many times the SPO2 has exceeded the safety limit set for the current session. The lower limit for blood oxygen saturation is set for each session in line with its objective. Whenever the limit is exceeded, the software alerts the user to remove their mask and recover in normoxia until they receive a new notification to put the mask back on.

